# Abbreviations

| API | approximal plaque index |
| --- | --- |
| MPD | maximum probing depth |
| mod. SBI | modified sulcus bleeding index |
| OHIP-G14 | Oral Health Impact Profile-Germany 14 |
| PBI | papillary bleeding index |
| PSI | periodontal screening Index |
| TI | Turesky plaque index |

## 1.2 Summary

Facial nerve palsy lead to immobility of the affected side of face (Trepel, 2017). Assumable, food residues on tooth surfaces cannot be removed by natural self-cleaning mechanisms such as targeted muscle movements or saliva, which are described in literature (Elferich & Tittmann, 2004). In addition to food intake, oral hygiene is impaired in patients (Jakobsen & Sticher, 2015). Deterioration of oral hygiene increases the risk of oral infections and consequently of other diseases (Hellwege, 2018).

Aim of this study is to investigate the oral health and oral health-related quality of life of patients with different forms of facial nerve palsy, as well as oral health in relation to facial nerve palsy variables such as disease duration and cause, which are collected as part of routine investigation at Facial Nerve Centre Jena.

In a controlled cross-sectional study, oral health parameters and oral health-related quality of life will be investigated at one time. Since patients in different temporal stages (acute phase, chronic phase) are to be documented, the setting of the Ears-, Nose- and Throat (ENT-) clinic Jena was chosen. There are both patients, with acute paresis and patients with chronic forms of facial nerve palsy. Oral health parameters and oral health-related quality of life of these patients groups should be compared with a control group. For this, controls without facial nerve palsy ever diagnosed by a doctor will be matched with corresponding patients according to age and gender.

Primary criterion for assessment of oral health will be the assessment of periodontal health, which will be analysed by a dentist using parodontal screening index (PSI; Hellwege, 2018; Weber, 2017). Other established indices are used to record caries and plaque incidence, bleeding tendency of gingiva, abnormalities of oral mucosa and presence of halitosis. These indices are compared between the two groups. Oral health-related quality of life will be assessed using the validated OHIP-G14- questionnaire (John, 2002; Slade 1997).

It is assumed a case number of 60 patients and 60 controls.

Both study groups will be recruited from ambulance level and ward level of ENT-clinic at Jena University Hospital. For better comparability, further controls can be recruited from the tinnitus centre of ENT-clinic Jena as well as from dental practices established in Thuringia.

## 1.3 Synopsis

| **Title of the study** | Oral health and oral health-related quality of life of patients with facial nerve palsy at Jena University Hospital |
| --- | --- |
| **Short name of the study (acronym)** | Oral health and oral health-related quality of life |
| **Head of study** | Priv.-Doz. [name] [name] |
| **further head of study** | Priv.-Doz. Dr. med. dent. [name] |
| **Investigator** | cand. med. dent [name] |
| **Indication/target population/disease** | Controls: healthy persons without facial nerve palsy ever diagnosed by a doctor  Patients: patients with different forms of facial nerve palsy in different temporal stages/ with different disease duration |
| **Study design/methodology** | Controlled cross-sectional study |
| **Clinical trial objectives/Objectives** | Primary objective:  To record oral health and oral health-related quality of life in patients and controls:  - To record dental status  (tooth mobility, restorations)  - To assess periodontal health  (PSI, presence of calculus, attachment loss and MPD)  - Assessment of gingiva bleeding  - Assessment of caries  (PUFA index and caries activity)  - Assessment of plaque infestation  (TI and API)  - Detection of oral mucosal abnormalities  - Detection of halitosis  Secondary objective:  - To assess oral health-related quality of life |
| **Target variables/criteria/endpoints** | Primary target variable:  PSI (chronic periodontitis parameter).  MPD (maximum probing depth)  mod. SBI (parameter for bleeding tendency)  PBI (parameter for quantity of papillary bleeding)  PUFA (parameter for odontogenic infections due to untreated caries)  API (parameter for approximal / interdental plaque infestation)  TI (parameter for plaque infestation)  Secondary target variable:  Oral health-related quality of life |
| **Number of participants** | 60 patients an 60 controls |
| **Total number of participants** | n=120 |
| **Inclusion criteria** | Controls: no history of facial nerve palsy, matched with patients according to age and gender  Patients: patients with all forms of facial nerve palsy (diagnosed by a doctor) |
| **Exclusion criteria** | Multimorbid patients/controls  Lack of informed consent  Edentulous patients/controls  Patients/controls with following diagnosed diseases:  - Haemophilia A and B  - Epilepsy  - AIDS |
| **Treatments/procedures, treatment plan (incl. follow-up)** | For controls and patients at one time:  - Informed study consent  - Completion of an initial questionnaire (questionnaire 1, subjective assessment of own oral hygiene and oral health)  - Oral health examination  - Completion of a second questionnaire (OHIP-G14 questionnaire on oral health-related quality of life)  - No treatment of patients and no follow-up care within the study, but within the individually annual dental check-up |
| **Schedule (study duration)** | Start: 01.05.2020  End: 30.12.2023  Patient-related:  Duration of study-related examination:  60 minutes |
| **Study sites** | n = 1 |
| **Statistical methods** | Descriptive statistics and interference statistics |
| **Funding** | Home remedies |

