## 6.7 Comparison of results

Data are first compared between patients and secondary with those of controls.

Comparisons are made with regard to oral health parameters:

- per patient:

- paretic and non-paretic side of mouth

- per controls:

- right and left side of mouth

- between patients:

- both halves of total mouth

- paretic side of mouth

- non paretic side of mouth

- between patients and controls:

- both sides of total mouth

- paretic side of mouth with corresponding side of mouth of control person

- non-paretic side of mouth with corresponding side of mouth of control person

- compared in terms of data from questionnaires:

- answers to each question between patients

- answers to each question between controls

- answers to each question between patients and controls

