# 7 Biometrics and sample size planning

A similar study demonstrating that peripheral facial nerve palsy impairs food intake and worsens oral hygiene, which may lead to oral diseases, was conducted at Nabon University Itabashi Hospital and Nihon University Dental Hospital in Japan from 2009 to 2011. This study included 30 patients and 30 controls. The planned study is based on this.

The necessary number of participans was determined with the Institute for Medical Statistics, Informatics and Data Science Jena. The programme G*power was used. Following values were assumed when calculating the exact number of cases:

- Wilcoxon-Mann-Whitney test (two groups)
- Tail: two
- parent distribution: min ARE
- effect size d: 0.6666667
- α err prop: 0.05
- Power (1-β err prop): 0.8
- allocation ratio N1/N2: 1

Thus, a case number of 43 patients and 43 controls was calculated. This makes a total number of 86 participants. To take drop-out cases into account, a total number of 120 subjects (60 patients/controls per group) is assumed.

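### Section 1.2 names PSI as the one primary criterion, the synopsis lists seven primary variables, and Section 7 sizes a single test at undivided 0.05 without naming its endpoint

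*Protocol*

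**What the plan says.** Section 1.2 (Summary) is specific: "Primary criterion for assessment of oral health will be the assessment of periodontal health, which will be analysed by a dentist using parodontal screening index". It then sets the remaining measures apart: "Other established indices are used to record caries and plaque incidence, bleeding tendency of gingiva", together with mucosal findings and halitosis. On this text there is one primary variable.

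Section 1.3 (Synopsis), in the row on target variables, reads differently: "Primary target variable: PSI (chronic periodontitis parameter). MPD (maximum probing depth) mod. SBI (parameter for bleeding tendency", then "PBI (parameter for quantity of papillary bleeding) PUFA (parameter for odontogenic infections due to untreated caries", then "API (parameter for approximal / interdental plaque infestation) TI (parameter for plaque infestation". That makes seven primary variables: PSI, MPD, mod. SBI, PBI, PUFA, API and TI. They include the bleeding, caries and plaque indices that 1.2 sets apart from the primary criterion. In the row on objectives, the synopsis names oral health-related quality of life in the primary objective and again as the secondary objective. Section 3.2 has it as secondary only.

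Section 3.1 places all the indices under the primary aim, gives periodontal health particular emphasis, and plans to compare the individual parameters with controls. It sets no order among them.

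Section 7 gives the inputs of one calculation, a "Wilcoxon-Mann-Whitney test (two groups"): two-sided, alpha 0.05, power 0.8, d = 0.6666667, minimum ARE, 1:1 allocation. The result is 43 per group, raised to 60 per group for drop-out. No endpoint is attached to d.

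**The concern.** The sample size belongs to one hypothesis test, but a reader cannot tell which one. Under 1.2 it would be PSI. Under 1.3 any of seven indices may be reported as a primary result. If none is singled out before analysis, the study can present worse oral health on whichever index reaches significance, and the nominal 5% no longer describes the risk of a false primary claim. If the seven are kept and alpha is divided among them, the calculation in Section 7, done at undivided alpha, no longer describes the power for a given index.

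**Working it through.** **Inputs.** From Section 7: d = 0.6666667, two-sided alpha 0.05, power 0.80, 1:1 allocation, minimum ARE (0.864 in G*Power), 43 calculated and 60 planned per group. From 1.3: seven primary variables. The protocol gives no correlations between the indices, so a common correlation from 0 to 0.9 is assumed.

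**1. Reproduce the plan's figure.** G*Power's ARE method uses a noncentral t distribution with df = 2n × 0.864 − 2 and noncentrality d × √(0.864 n / 2).

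- n = 43: df = 72.3, noncentrality = 0.6667 × √18.576 = 2.873, power 80.9%.
- n = 42: power 79.98%, just short.

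So 43 per group is correct for one test at undivided 0.05. The calculation itself contains no error.

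**2. Reading of 1.2: PSI alone.** The 5% error rate holds and power is 80.9% at 43 per group, provided that d = 0.667 is a fair assumption for PSI.

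**3. Reading of 1.3: seven tests, each at 0.05, no adjustment.** With independent tests the chance of at least one false positive is 1 − 0.95^7 = 0.302. For correlated tests, seven equicorrelated normal statistics were simulated (400,000 draws):

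| Assumed common correlation | 0 | 0.3 | 0.5 | 0.7 | 0.9 |
|---|---|---|---|---|---|
| At least one false positive | 30% | 27% | 23% | 18% | 11% |

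High correlations are plausible for some pairs: mod. SBI and PBI both record bleeding, API and TI both record plaque. The whole range therefore has to be shown. It stays above 5% throughout.

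**4. Reading of 1.3: seven tests with Bonferroni.** Alpha per index is 0.05 / 7 = 0.00714. Same method as in step 1, power for one given index:

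| Evaluable per group | 43 | 60 | 67 | 68 |
|---|---|---|---|---|
| Power | 54.4% | 74.0% | 79.9% | 80.7% |

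Even with no drop-out at all, 60 per group falls short of 80% for a given index; 68 evaluable per group would be needed. The drop-out allowance implied by Section 7 is 1 − 43/60 = 28.3%. At that rate, 68 evaluable means 68 / (43/60) = 94.9, or about 95 recruited per group.

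**5. Other success rules.** The protocol states none, so two are shown for scale.

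- At least one of seven significant under Bonferroni, if all seven truly had d = 0.667 (normal approximation): more than 99% at 43 per group with independent indices, about 96%, 92% and 85% at correlations 0.3, 0.5 and 0.7, and about 74% at 0.9. At 60 per group it is about 88% or more throughout.
- All seven significant at 0.05 with 80% power each: 0.8^7 = 21% if independent, rising to about 67% at correlation 0.9.

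**The case against.** The strongest reply is that Section 1.2 already answers the question. With PSI as the only primary criterion, 5% and 80.9% both hold and the synopsis list is loose drafting. That is right as far as it goes, and it is why the remedy is wording only. It does not remove the contradiction, because 1.3 says otherwise in plain terms, 3.1 does not decide between them, and Section 7 names no endpoint.

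A reader might infer that the stated error rate and power both fail for the primary result. The documents do not support this. On the reading of 1.2 neither fails. On the reading of 1.3 they do not fail together under one rule: unadjusted testing breaks the 5%, and Bonferroni judged index by index breaks the 80%. Nor does correction always cost the 80%. If all seven indices carried the effect and one significant index sufficed, power at 43 per group would exceed 80% for the assumed correlations up to 0.7. The protocol neither states that rule nor ties d to any index, so this cannot be relied on either.

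A reader might also see a further contradiction in Section 6.7: "Data are first compared between patients and secondary with those of controls". This can simply mean the order in which analyses are run. It does not conflict with a sample size built on patients versus controls, and no weight is placed on it here.

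Finally, a multiplicity rule may stand in an SAP that is not shown, so its absence from the protocol is not the point. An SAP rule would not make 1.2 and 1.3 agree, and dividing alpha there would not change a sample size fixed at undivided alpha. It is also fair to say that this is an observational study whose stated aims are largely to record and describe. But it plans inferential statistics and fixes alpha and power for a test, so the test needs a named endpoint.

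**Conclusion.** The point holds as an unresolved contradiction about the primary endpoint, not as a wrong calculation. If 1.2 governs, the design is adequate as sized, subject to d = 0.667 applying to PSI. If 1.3 governs without adjustment, the risk of at least one false-positive primary result is about 11% to 30%. If 1.3 governs with Bonferroni, power for a given index is 54% at 43 and 74% at 60 per group. These figures rest on the plan's own inputs, with d = 0.667 applied to every index, and on assumed common correlations between 0 and 0.9. The double placing of oral health-related quality of life in the synopsis is a smaller inconsistency of the same kind.

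**What to change.** Make Sections 1.2, 1.3, 3.1 and 7 name the same single primary endpoint and contrast: PSI, as 1.2 already says, in patients versus matched controls, two-sided at 0.05. Move MPD, mod. SBI, PBI, PUFA, API and TI to secondary or exploratory status. List OHIP-G14 as secondary only, in line with 3.2.

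In Section 7, state which variable d = 0.667 was derived for. The protocol does not say, so it should not simply be declared to be PSI. If it came from another variable, derive the effect size for PSI and restate the power.

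If the sponsor prefers to keep seven primary variables, the success rule has to be stated and the sample size recalculated for it.

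Putting the patient-control comparison first in 6.7 would help readers but is optional.

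Cost: protocol wording and, if d does not refer to PSI, one recalculation. No extra participants are needed if d does refer to PSI. The downside is that six indices can no longer be presented as primary results.

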# 2 Background

## 2.1 Initial situation

In facial nerve palsy, a distinction is made between peripheral and central paresis depending on the location of damage (Kaschke, Behrbohm & Nawka, 2009). Main symptom of both forms of facial nerve palsy is a flaccid paralysis of facial musculature (Trepel, 2017). Perioral region is affected in both supranuclear damage, which leads to central palsy, and infranuclear damage, which results in peripheral palsy (Jakobsen & Sticher, 2015). In the patient’s cheek region, muscle tension in the buccinator muscle is missing or too high, which can result in bite injuries in patient's cheek region. In addition, there is a risk that, in absence of cheek activity and sensitivity, food residues remain in the buccinator pocket after food intake, which, among other things, favours the development of inflammations of mucosa (Jakobsen & Sticher, 2015). In the area of lip musculature, flaccid paralysis of the facial musculature leads to a drooping corner of mouth on the affected side and incomplete lip closure. For example, when drinking, patients are therefore unable to hold the liquid in their mouth (Trepel, 2017). Damage to facial nerve in the facial nerve canal in front of tympanic chord may also lead to dry mouth (Trepel, 2017). However, saliva in particular, in addition to targeted muscle movements, provides a natural self-cleaning mechanism of oral cavity when food residues remain on tooth surfaces (Elferich & Tittmann, 2004). If there is too less saliva, resulting in a lower saliva flow rate, risk of caries increases. Severe xerostomia can lead to dehydration of oral mucosa. Consequently, tears, lesions and pain occur (Elsäßer & Ludwig, 2017). Xerostomia can lead to a significant reduction in quality of life over a longer period of time (Zenk, Leins & Bozzato, 2005).

Due to changes in facial area and especially due to restrictions in mobility of the perioral region, food intake, but also oral hygiene is impaired in affected patients (Jakobsen & Sticher, 2015). If there is incomplete lip closure and patients have difficulty keeping liquids in their mouths, it can be assumed that those affected also have problems rinsing their mouths after cleaning their teeth, spitting out toothpaste or using mouth rinses. If patients' oral care is more difficult, then the question arises whether this also worsens the resulting oral hygiene and associated oral health in patients. A study published in 2013 provides the first indication that peripheral facial nerve palsy impairs oral hygiene, which can subsequently lead to oral diseases (Kato et al., 2013).

## 2.2 Research question and justification

Due to the lack of evidence, the question remains as to what exactly oral hygiene looks like in patients with facial nerve palsy, whether deficits in oral health becomes apparent due to more difficult conditions of oral care, whether these correlate with the duration of the disease, whether differences in oral health between paretic and non-paretic side can be recorded and whether differences can be detected in comparison to non-diseased controls.

A lack of oral hygiene is initially reflected by dental diseases such as caries and diseases of periodontium. Foeter ex ore (bad breath), an increased bleeding tendency of gingiva, gingiva swelling and pain represent consequences (Elsäßer & Ludwig, 2017). In further course, deterioration of oral hygiene and resulting pain in oral cavity make it more difficult to eat, because only with a healthy oral cavity is it possible to do so in the best possible way (Elferich & Tittmann, 2004). But it is not only because of latter facts that a deterioration in oral hygiene represents a great risk for patients. As early as 2002 on a press conference in Berlin, the German Dental Association used the slogan "Healthy teeth - healthy body" to illustrate interactions between bacterial diseases of periodontium and cardiovascular diseases as well as diseases of the blood vessels (Elferich & Tittmann, 2004). In examined preparations of corresponding vascular walls, detection of periodontal pathogens was successful. It has been shown that microorganisms occurring in periodontitis are associated with arteriosclerosis (Mastragelopulos, et al., 2004). Periodontal pathogenic microorganisms lead to activation of platelet aggregation, promote the production of inflammatory molecules, as well as formation of foam cells from macrophages, leading to accumulation of atherosclerotic plaque in vessel walls (Jacek, 2018). Connective tissue of gingival margin has a dense, highly permeable subsulcular vascular network (Hellwege, 2018). When periodontium is destroyed, bacteria can enter the bloodstream via resulting gingival pockets, where they can endanger the systemic health of patients (Jacek, 2018). But it is not only via gingiva that microorganisms can spread throughout body. Silent aspiration, which is associated with an increased risk of pneumonia, as well as cracked mucous membranes are considered other possible routes of spread (Elsäßer & Ludwig, 2017). It becomes clear that oral infections can be the starting point for development of further diseases (Hellwege, 2018). In addition to already described interaction with atherosclerosis, links to diseases endocarditis, coronary heart disease and stroke, among others, are assumed. A correlation with insulin requirements of diabetics and complications in pregnancy is also suspected (Hellwege, 2018). It should be noted that with help of better dental health, general health can benefit. The quote by Klaus-Dieter Hellwege from the book *“Praxis der zahnmedizinischen Prophylaxe”* (The Practice of Dental Prophylaxis), published by *Thieme Verlag* in 2018, concluded: "With clean and healthy teeth, life is not only better, but also longer." (Quote, Klaus-Dieter Hellwege, 2018, Chapter 3, p.47). Furthermore, good oral hygiene makes a positive and decisive contribution to well-being and quality of life (Elsäßer & Ludwig, 2017).

Based on the above considerations, the following hypothesis can be formulated: If good oral hygiene can no longer be achieved due to impeded oral care, this leads to patient discomfort. Aided by the inhibited possibilities of oral care, food intake and fluid intake, the affected patients distance themselves from their social environment (Jakobsen & Sticher, 2015).

In summary, on the one hand it becomes clear that good oral hygiene and oral health have great relevance for a high quality of life, participation in everyday life and a healthy systemic and psychological set-up. On the other hand, it can be stated that a deterioration of oral hygiene has far-reaching consequences for health and such a situation should be recognized and treated promptly. Especially in predilection sites such as fissures, active plaque can be deposited and, if removed irregularly and delayed, can lead to demineralisation on tooth surface. Resulting caries lesions are irreversible (Roulet, Fath, & Zimmer, 2017).

Based on above-mentioned indications that oral hygiene and associated oral health could be impaired in patients with facial nerve palsy due to the fact that oral care is more difficult and that self-cleaning mechanisms are restricted, an overview of oral health of patients with facial nerve palsy at Jena University Hospital is to be created. If possible deficits and differences to non-affected persons can be uncovered, it will be possible to derive a need for dental therapy, to specifically address this patient group in the future and to improve their oral hygiene and associated general health.

# 3 Objectives

## 3.1 Primary objective

The primary aim of the study is to examine and record oral health of patients with different forms of facial nerve palsy and document their oral health in relation to facial nerve palsy variables such as duration and cause of disease, which are collected as part of routine investigation of the Facial Nerve Centre Jena. Special attention will be paid to periodontal health of patients. In order to record oral health, a complete dental status including existing restorations and tooth mobility should be collected. To assess periodontal and gingival health, PSI (parameter for chronic periodontal disease, developed by the German Society of Periodontology 2002, cf. Hellwege 2018), presence of calculus, maximum probing depth (in mm), attachment loss (in mm), mod. SBI according to Lange et al. 1986 (parameter for occurrence of sulcus haemorrhage, cf. Weber 2017) as well as PBI according to Saxer and Mühlemann 1975 (parameter for determining the quantity of papillary haemorrhage, cf. Hellwege 2018) should be determined by a dentist. As further oral health parameters, caries and plaque infestation should be documented. Caries infestation is to be determined using PUFA index according to Monse et al. 2010 (parameter for odontogenic infections due to untreated caries, cf. Kühnisch & Heinrich-Weltzien, 2020) and recording of caries activity. Plaque infestation is examined with TI (Turesky et al. 1970, parameter for plaque infestation, modification of plaque index according to Quigley and Hein 1962, cf. Peter Gängler et. al 2005) and API according to Lange et al. 1986 (parameter for approximal/interdental plaque infestation, cf. Weber 2017). In addition, oral mucosa should be inspected thoroughly and presence of halitosis assessed using organoleptic diagnostics (cf. Weber 2010).

This will provide a comprehensive overview of oral situation in patients with facial nerve palsy. Individual oral health parameters will be compared with a control group, which will be examined with regard to same measurement procedures.

